### Data Analysis

The principal analyses will involve the comparison of average scores of pain at rest in the first 12 hours post-operation between the ropivacaine pump infusion and placebo patients using an intention-to-treat analysis. This will be performed by multiple regression adjusting for infusion type and type of operation. Similar analyses will compare maximal pain at rest in the first 12 hours and average and maximal pain at rest in the second 12-hour post-operative period. Sensitivity analyses to assess dependence upon potential baseline imbalance in prognostic factors will also be performed. Other secondary outcome analyses will include amount of morphine administered, the incidence of complications, late discharge from hospital (>1 bed day) following ASD, early or late discharge (< or > 2 bed days) following RCR, and the incidence of post-operative adhesive capsulitis up to 2 or 4 months following ASD or ASD plus RCR respectively. Further analyses will assess differences between arms in maximum and average pain scores at rest adjusted for amount of opioid used.

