In our setting, post-operative pain management has traditionally consisted of pre-emptive local anaesthetic (ropivacaine) and post-operative PCA opioids. Recently and concurrently, both intra-operative intravenous parecoxib a selective COX-II inhibitor, and direct operative ropivacaine infusion pumps were introduced as standard practice although evidence for their added benefits is limited. The disposable pump with single or dual catheters and ropivacaine costs $AUD300–600 and $155 respectively (at time of publication), while a single pre-emptive bolus of 20 mls 1% ropivacaine costs $20 and an IV bolus of parecoxib (40 mg) costs only $25. Reported adverse effects of infusion pumps include difficulty in removal of the catheter, too rapid delivery of the drug, leakage with local contamination, and breakage of the catheter tip leaving a remnant in the joint [22,23]. To warrant continued use of the ropivacaine infusion, it would need to be demonstrated that its benefit/s in terms of pain relief, reduction in drug-related adverse effects, earlier shoulder mobilisation and/or reduced hospital stay is/are worth the additional costs.

The aim of this randomised placebo controlled trial is to determine the efficacy and safety of a continuous infusion of ropivacaine 0.75% (Naropin – AstraZeneca) delivered by a single catheter 'Painbuster'(I-Flow Corporation, Lake Forest, USA) pain management system when used following elective arthroscopic rotator cuff surgery. Our hypothesis is that continuous infusion of local anaesthetic following rotator cuff surgery would be equivalent to pain relief provided by a placebo in the setting of pre-emptive ropivacaine, intra-operative parecoxib and post-operative intravenous morphine and oral dextropropoxyphene hydrochloride/paracetamol available on demand.

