### Sample Size

Sample size is based upon clinical equivalence being deemed as a difference in mean pain scores of +/-1 point on a 10 point scale. That is, any difference between groups of 1 point or less will be regarded as equivalent for practical purposes. Statistically, equivalence will be declared if the 90% CI for the difference in mean pain scores between the groups lies entirely within the interval -1 to +1. To have 80% probability that this equivalence will occur when the two infusion therapies are actually exactly equivalent requires 70 patients per arm, assuming a standard deviation of 2 points within each arm (obtained from pilot work). This sample size will also be able to detect a difference of 0.95 points with 80% power and a two-sided 5% significance level. Allowing for 10% dropout, the sample size is inflated to 78 patients per group.

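### The equivalence conclusion rests on an intention-to-treat comparison with no planned analysis of undelivered infusions, which shrink the difference in favour of the trial's hypothesis

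*Protocol article*

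**What the plan says.** The Background of the protocol article states the hypothesis that "continuous infusion of local anaesthetic following rotator cuff surgery would be equivalent to pain relief provided by a placebo", given the bolus, parecoxib and on-demand analgesia that all participants receive. Sample Size sets the margin ("clinical equivalence being deemed as a difference in mean pain scores of +/-1 point on a 10 point scale") and the rule: "equivalence will be declared if the 90% CI for the difference in mean pain scores between the groups lies entirely within the interval -1 to" (the upper limit being +1).

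Data Analysis fixes the principal comparison of average rest pain over the first 12 hours "between the ropivacaine pump infusion and placebo patients using an intention-to-treat analysis", by multiple regression on infusion type and operation type. It then names sensitivity analyses for baseline imbalance in prognostic factors, and further pain analyses adjusted for opioid use. It names no per-protocol or as-treated set, and no analysis that takes account of whether the infusion was delivered.

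The Background acknowledges device problems: "Reported adverse effects of infusion pumps include difficulty in removal of the catheter, too rapid delivery of the drug, leakage with local contamination". It also mentions that a catheter tip can break. It gives no rates.

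**The concern.** In a superiority trial, participants who do not receive the active treatment pull the arms together and make a positive finding harder to reach, so intention-to-treat errs on the cautious side. In an equivalence trial the same dilution makes the hypothesised result easier to reach. Here an active-arm pump that leaks leaves its patient close to the placebo condition, while a saline pump that leaks changes little. Non-delivery therefore moves the estimate toward zero, which is where the trial expects to find it.

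At stake is how a positive result is read. The Discussion would take equivalence to mean that the device contributes nothing beyond existing pain management. Without an analysis of delivered infusions, an ineffective drug and an effective drug that did not reach the subacromial space would look the same.

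**Working it through.** **Inputs from Sample Size.** Margin ±1; 90% confidence interval; SD 2 per arm ("assuming a standard deviation of 2 points within each arm (obtained from pilot work"); 70 per arm for 80% probability at zero true difference ("To have 80% probability that this equivalence will occur when the two infusion therapies are actually exactly equivalent requires 70 patients per arm"). The non-delivery fraction f is an assumption, because the article gives none.

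**The plan's own figures.**
- Normal approximation: n = 2 × [SD × (z₀.₉₅ + z₀.₉₀) / margin]² = 2 × [2 × (1.645 + 1.282) / 1]² = 68.5, so 69 per arm.
- Using the t distribution, power is 79.9% at 69 and 80.6% at 70, so 70 is reproduced.
- Dropout: 70 / 0.90 = 77.8, so 78 per arm.

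There is no arithmetic error here.

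**When equivalence is declared.** SE = 2 × √(2/70) = 0.338. The interval lies within ±1 when the observed difference is smaller in size than 1 − 1.645 × 0.338 = 0.444.

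**Effect of non-delivery.** Suppose a delivered infusion has effect D, a fraction f of active-arm pumps delivers no drug, failure is unrelated to outcome, and the SD stays at 2. The intention-to-treat difference is then d = (1 − f) × D, and

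P(declare equivalence) = Φ((0.444 − d)/0.338) − Φ((−0.444 − d)/0.338).

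For example, at D = 1 and f = 10%, d = 0.9: (0.444 − 0.9)/0.338 = −1.35, giving 8.9%; the second term is negligible.

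| Assumed f | d if D = 1.0 | False equivalence, D = 1.0 | False equivalence, D = 1.25 |
|---|---|---|---|
| 0% | 1.00 | 5.0% | 0.9% |
| 2% | 0.98 | 5.6% | 1.0% |
| 5% | 0.95 | 6.7% | 1.4% |
| 10% | 0.90 | 8.9% | 2.2% |
| 20% | 0.80 | 14.6% | 5.0% |

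The t-based calculation agrees to within about 0.1 percentage point.

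**Power of a per-protocol set at zero true difference.** With 10% excluded, 63 per arm remain: SE = 2 × √(2/63) = 0.356, and power = 2 × Φ(1/0.356 − 1.645) − 1 ≈ 75%. With 5% excluded (66 per arm) the t-based figure is 77.5%; with 20% excluded (56 per arm) it is 67.5%. If both analyses had to meet the margin, joint power with 10% excluded from each arm would be about 73% by simulation.

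**The case against.** **The policy question.** Much of the article asks whether the pump is worth paying for as it is used, and the aim names the infusion as delivered by that device. Device failures then belong to the strategy, intention-to-treat answers directly, and its 5% error holds. This stands. A reader might infer that intention-to-treat is the wrong principal analysis or that the trial's error rate is uncontrolled; the article supports neither. What remains is that both arms receive a pump and the hypothesis concerns the infused anaesthetic, so the delivered effect is also in question.

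**Silence on other sets.** This is a condensed article and the SAP is not shown. Data Analysis does not exclude a per-protocol set, and a reader should not infer that it does. The point rests on what is stated: the principal analysis is fixed, and the analyses listed beside it do not address delivery.

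**The device problems.** A reader might take the Background list as a catalogue of delivery failures. Only leakage clearly is one, and tip breakage arguably. Difficult removal is not failed delivery, and over-rapid delivery need not draw the arms together.

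**Size.** The first false-equivalence column takes the least favourable true effect and all-or-none delivery. Catheter position is verified under vision, and the endpoint covers 12 hours of a supply lasting 180/5 = 36 hours, so failure may be rare. Below about 2% the effect is negligible.

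**The remedy.** Exclusions for pump function come after randomisation and may depend on pain or recovery. This argues against giving the per-protocol result an outright veto, but not against reporting it.

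**Conclusion.** The concern holds in a limited form. The planned analysis leans toward the trial's own hypothesis with respect to the effect of a delivered infusion, and no listed analysis would show it. For a delivered effect exactly at the margin, false equivalence is about 6.7% at 5% non-delivery, 8.9% at 10% and 14.6% at 20%, against a nominal 5%. For a delivered effect of 1.25 points it reaches 5% only at 20%. These figures assume SD 2, 70 per arm, complete failure when delivery fails, and failure unrelated to outcome; the rates themselves are assumed. The direction of the bias is certain under these assumptions, but its size in this trial is unknown. This is a cheap improvement to the plan. It does not invalidate the design or the sample size calculation.

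**What to change.** Keep intention-to-treat as the principal analysis. In Data Analysis, add a per-protocol analysis of the primary endpoint, with the set defined before unblinding: allocated infusion started and, from blinded records, delivered through 12 hours. Report its 90% confidence interval against ±1 beside the intention-to-treat interval, with the number and reasons for exclusion by arm.

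State the reading in advance. Claim that the infused drug adds nothing only if the two analyses agree. If only intention-to-treat meets the margin, limit the conclusion to the pump strategy as used.

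The cost is a few sentences of analysis wording and a blinded record of pump and catheter function to 12 hours. The per-protocol set is smaller, with about 75% power at 63 per arm, and its exclusions may themselves bias the comparison, so it should be read beside intention-to-treat and not in its place. No larger sample is required if it is supportive. Keeping 70 evaluable per arm after 10% dropout and a further 10% exclusion would need 70/(0.9 × 0.9) = 86.4, so 87 per arm.

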### Setting and Participants

Participants will be recruited from the private community-based practice of a single orthopaedic shoulder surgeon in Melbourne, Australia. The decision to include only one surgeon will eliminate any potential confounding of results due to differences in surgical skill, technique and care across treatment arms. One of two elective operations will be performed based upon diagnostic arthroscopy at the time of operation: ASD or ASD plus RCR. All rotator cuff surgery will be performed at either the Mercy Private Hospital or Linacre Private Hospital in Melbourne, Australia.

All consecutive, eligible patients who fulfil selection criteria will be offered study participation. Inclusion criteria will be adults aged 18 years or over in whom elective subacromial decompression or rotator cuff repair is planned. Exclusion criteria will be: (i) patients with massive or irreparable rotator cuff tears; (ii) patients requiring grafts to fill the defect; (iii) previous injury or surgery to the shoulder i.e. fracture or revision surgery; (iv) previous mastectomy on the affected side; (v) peripheral neuropathy affecting the upper limbs; (vi) chronic opioid use; (vii) morbid obesity (body mass index greater than 35 kg per metre squared); (viii) Parkinson's disease; (ix) pregnancy; (x) contraindication to parecoxib including aspirin sensitive asthma, history of recent gastric or duodenal bleeding, severe renal impairment or sulphonamide allergy; (xi) inability to understand written and/or spoken English.

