### Outcome assessment

All assessors collecting and assessing outcome will be blinded to treatment allocation. One assessor will perform all baseline, and 2 or 4 month (JC) assessments. Post operative assessment of pain, analgesia and duration of hospital stay will be recorded by nursing staff.

Baseline data will include gender, age at operation, dominance, side of operation, height, weight, history of diabetes, employment, duration of symptoms and compensation status. As a verbal analogue pain scale (VAPS) will be used to measure pain postoperatively, participants will be taught to use the scale at the time of pre-operative baseline assessment to measure current level of pain at rest. The VAPS is an 11-point scale where 0 = no pain and 10 = worst pain imaginable.

Outcomes will be assessed post operatively at 15, 30 and 60 minutes, 2, 4, 8, 12, 18 and 24 hours, and 2 or 4 months for ASD or ASD and RCR respectively. Average pain at rest and maximal pain over the first and second 12 hour post-operative periods, will be computed using the VAPS. The amount of rescue medication used over the first and second 12 hour post-operative periods will be computed as intravenous opioid intake in mgs and oral analgesic intake as a tablet count.

Range of movement of the shoulder will be measured at baseline and at 2 or 4 months for ASD or ASD plus RCR respectively. Active shoulder movements will be measured according to a standardised and reliable protocol [24]: Total shoulder flexion (TSF), total shoulder abduction (TSA) and external rotation in neutral (ERN) will be measured with a gravity inclinometer (in degrees) and internal rotation will be assessed by measuring distance (in centimetres) from the base of the occiput to how high the hand will reach up behind the back (HBB). Post-operative adhesive capsulitis will be defined as having symptoms of shoulder pain and stiffness and restriction of movement of at least 30° in two or more planes at 2 or 4 months post-operatively for ASD or ASD plus RCR respectively.

Length of hospital stay will be measured in days from time of surgery and all adverse effects will be recorded.

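### Adding pre-operative pain at rest to the primary regression would probably narrow the 90% CI that decides equivalence, at a cost of one degree of freedom

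*Protocol article*

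**What the plan says.** All references are to the protocol article.

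- **Primary model (Data Analysis).** "This will be performed by multiple regression adjusting for infusion type and type of operation". Infusion type is the treatment term, so operation type is the only covariate. It is also the only stratification factor named under Randomisation. The same section plans similar analyses for the other pain endpoints, and separate sensitivity analyses that look at chance baseline differences in prognostic variables, none of them named.
- **Baseline pain (Outcome assessment).** "participants will be taught to use the scale at the time of pre-operative baseline assessment to measure current level of pain at rest". The scale runs from 0 to 10 and is the one used after surgery. The itemised list of baseline variables in that section does not include the score.
- **Decision rule (Sample Size).** "equivalence will be declared if the 90% CI for the difference in mean pain scores between the groups lies entirely within the interval -1 to" (the upper limit being +1).
- **Planning values (Sample Size).** Power is 80% "when the two infusion therapies are actually exactly equivalent requires 70 patients per arm". The spread behind this figure is given in the same sentence: "assuming a standard deviation of 2 points within each arm (obtained from pilot work". No reduction in SD is taken for any covariate.

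**The concern.** The trial's answer rests on the width of one interval. Equivalence is declared only if the whole 90% CI fits between -1 and +1, so a covariate that explains outcome variance raises the chance of a clear answer at the same number of patients. A pre-operative rating of the same symptom on the same scale is the obvious candidate, and it is missing from a covariate list that the article has already fixed.

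Precision also matters because the planned power is calculated at a true difference of exactly zero. A small real effect, still well inside the range that the article calls equivalent, leaves less room for the interval. The planned sensitivity analyses do not help here, since they leave the primary interval unchanged.

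**Working it through.** **Inputs from Sample Size:** margin 1 point; 90% CI, so z = 1.645 on each side; SD 2 within each arm; 70 per arm; true difference 0.

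**Assumption, not in the article:** r, the correlation between baseline pain at rest and 0-12 hour average pain given operation type. I use 0.1 to 0.5. SD 2 is taken as the residual SD of the planned model.

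**Step 1: reproduce the plan's figures.**

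- Patients per arm for equivalence: 2 × [2 × (1.645 + 1.282) / 1]² = 68.5, so 69, against the stated 70.
- Standard error at 70 per arm: 2 × √(2/70) = 0.338. The 90% half-width is 1.645 × 0.338 = 0.556.
- Equivalence power: 2Φ(1/0.338 − 1.645) − 1 = 2Φ(1.313) − 1 = 0.811. Using the t distribution it is 0.806.
- Detectable difference (two-sided 5%, 80% power): (1.960 + 0.842) × 0.338 = 0.947, matching the stated 0.95.
- Dropout: 70 / 0.9 = 77.8, so 78 per group, as stated.

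The plan therefore reaches its own 80% target without baseline pain in the model.

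**Step 2: add baseline pain.** Residual SD = 2 × √(1 − r²). The standard error is SD × √(2/70). For a true difference d, power = Φ((1 − d)/SE − 1.645) + Φ((1 + d)/SE − 1.645) − 1, which at d = 0 is the formula of Step 1. The column for d = 0.25 illustrates a small true difference and is also an assumption. Power is by normal approximation.

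| r | Residual SD | 90% half-width | Power, d = 0 | Power, d = 0.25 | Per arm for 80% at d = 0 |
|---|---|---|---|---|---|
| 0 (planned) | 2.00 | 0.556 | 0.811 | 0.70 | 69 |
| 0.1 | 1.99 | 0.553 | 0.816 | 0.70 | 68 |
| 0.2 | 1.96 | 0.545 | 0.831 | 0.72 | 66 |
| 0.3 | 1.91 | 0.530 | 0.855 | 0.74 | 63 |
| 0.4 | 1.83 | 0.510 | 0.886 | 0.77 | 58 |
| 0.5 | 1.73 | 0.482 | 0.923 | 0.82 | 52 |

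At d = 0 the gain is 0.5 to 2 percentage points for r of 0.1 to 0.2, about 4 points at r = 0.3, and about 11 points at r = 0.5.

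**Step 3: the same check for hospital.** "All rotator cuff surgery will be performed at either the Mercy Private Hospital or Linacre Private Hospital", so hospital might also be considered. A two-level factor with mean difference D and a 50/50 split explains 0.25 × D² of a variance of 4. Neither D nor the split is in the article.

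- D = 0.25: 0.4% of variance, power 0.813.
- D = 0.5: 1.6% of variance, power 0.819.
- D = 1.0: 6.3% of variance, power 0.842.

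More uneven splits gain less. Up to a half-point difference, hospital adds less than one percentage point of power.

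**The case against.** The strongest reply is that nothing in the model is wrong. It is pre-specified, it contains the stratification factor, randomisation makes its treatment estimate unbiased, and the sample size takes no credit for covariates yet still gives 81% power. All of that stands, and it rules out reading the omission as a flaw that makes the analysis biased or underpowered.

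A second reply is that the benefit depends on a correlation that the article never gives. This also stands. Patients receive a pre-incision ropivacaine bolus, parecoxib and morphine on demand, and these could weaken the link between pre-operative and early post-operative pain. The relevant r is also the partial one, given operation type, because that term is already in the model. The low values of r therefore belong in the range, and at those values the gain is small. The reply does not remove the suggestion, because the cost is negligible even if r is low.

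A reader might go further in two ways that the article does not support.

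- **Hospital as an equal omission.** Hospital is not a stratum, there is one surgeon, and the Discussion describes a common post-operative regimen. That nurses at two sites record pain does not show that the sites differ, and Step 3 finds little to gain.
- **Covariates chosen after seeing the imbalance.** The Data Analysis section labels the imbalance analyses as sensitivity analyses and fixes the principal model separately, so they do not compete with the primary result. A condensed article may leave the choice of their variables to the analysis plan.

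**Conclusion.** The point holds as a low-cost improvement. The principal regression omits a same-scale baseline measurement that would probably narrow the interval deciding equivalence. At 70 per arm and no true difference, power would go from 0.81 to somewhere between 0.82 (r = 0.1) and 0.92 (r = 0.5), and the half-width from 0.556 to between 0.553 and 0.482. These figures rest on an assumed r, on SD 2 as the starting residual SD, and on the normal approximation.

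It would be too strong to say that precision is certainly lost, since the article gives no figure for r. It would also be too strong to say that the score is already secured in the data. The text describes rating pain at rest at the baseline visit, but the list of baseline variables does not name it.

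**What to change.** In Data Analysis, state the primary model as: average pain at rest over 0-12 hours = treatment + operation type + baseline pain at rest on the verbal scale. Say that the 90% CI for the treatment term from this model is the one compared with ±1. Use the same covariates for maximal pain over 0-12 hours and for average and maximal pain in the second 12 hours. In Outcome assessment, add the baseline pain score to the list of recorded baseline variables.

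The cost is a sentence or two of text and one degree of freedom among about 140 analysed patients (2 × 70). The sample size need not change.

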### Interventions

The surgeon's standard surgical protocol for rotator cuff surgery will be adhered to as follows: Participants will be asked to cease all NSAIDs two weeks prior to commencement of the study but will be allowed codeine, paracetamol or dextropropoxyphene. All operations will be performed under general anaesthesia using a standardised method consisting of propofol 2–2.5 mg/kg and fentanyl 1–2 mcg/kg as induction agents, nitrous oxide/oxygen 2:1, +/- isoflurane, morphine as required to maintain heart rate, blood pressure, respiratory rate within normal limits, and spontaneous ventilation on a laryngeal mask unless contra-indicated.

All patients will receive a total of 20 mls of 1% ropivacaine injected as a pre-emptive bolus dose into both the glenohumeral joint and the subacromial space fifteen minutes prior to insertion of the arthroscope. During the operation all patients will receive an intravenous bolus of 40 mg of parecoxib. At the conclusion of the surgery, all patients will have insertion of a 'Pain buster' catheter into the subacromial space with the position verified by direct or arthroscopic vision. According to blinded randomised treatment allocation the 'Pain buster' elastomeric pump will contain 180 mls of either 0.75% ropivacaine or an identical placebo of normal saline administered at 5 mls per hour.

All patients will have access to alternative analgesia for break through pain including both a PCA pump of intravenous morphine available on demand with a lock out period and dextropropoxyphene hydrochloride/paracetamol. All medications will be recorded.

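### The further analysis of pain adjusted for opioid use conditions on a post-randomisation outcome, so it cannot show whether rescue analgesia masked a benefit of the infusion

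*Protocol article*

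**What the plan says.** Under Interventions: "All patients will have access to alternative analgesia for break through pain including both a PCA pump of intravenous morphine available on demand". Rescue is therefore taken after allocation, in both arms, in response to pain.

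Under Outcome assessment: "The amount of rescue medication used over the first and second 12 hour post-operative periods will be computed as intravenous opioid intake in mgs", with oral analgesics counted as tablets. These are the same two windows over which average and maximal pain are computed.

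Rescue use is among the secondary end points, and Data Analysis repeats it: "Other secondary outcome analyses will include amount of morphine administered".

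The principal comparison is by intention to treat: "This will be performed by multiple regression adjusting for infusion type and type of operation". Opioid is not a covariate there. The equivalence rule in Sample Size rests on the 90% confidence interval for the difference in mean pain, with limits of -1 and +1.

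The last sentence of Data Analysis then adds: "Further analyses will assess differences between arms in maximum and average pain scores at rest adjusted for amount of opioid used". It comes with no estimand, assumption or caution.

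**The concern.** Opioid use in this trial is a consequence of pain, can be changed by the infusion, and itself lowers the recorded pain score. Using it as a covariate causes two problems. It blocks the part of the treatment effect that passes through opioid use. It also compares patients across arms who used the same amount of morphine, and if the infusion works, such patients differ in their underlying pain. Randomisation no longer protects that comparison.

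The question behind the analysis is a fair one, because on-demand rescue can narrow a real difference in pain. The trial's hypothesis is equivalence, and the Discussion says a finding of equivalence would support doing without the pump and saving its cost. A reader wondering whether rescue hid a benefit will turn to the one planned analysis that combines pain with opioid. If that analysis usually understates the effect, it reassures in the wrong direction.

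**Working it through.** **Design figures first.** Inputs from Sample Size: margin 1, SD 2, 90% interval, 80% power, true difference 0.
- Normal approximation: n = 2 × [2 × (1.645 + 1.282) / 1]² = 68.5, so 69 per arm.
- With the t distribution, power is 79.9% at 69 and 80.6% at 70, so the stated 70 is reproduced.
- Power for 0.95 points at 70 per arm is 80.2%, and 70 / 0.9 rounds up to 78.

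None of these figures is in dispute, and the point does not alter them.

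**Model for the adjusted analysis.** The article gives no pain-opioid relation, so everything here is assumed.
- Underlying pain: P = 5 - d·A + U, where A = 1 for ropivacaine and U has SD 2.
- Opioid, in arbitrary units: O = b·P + noise with SD s.
- Recorded pain: Y = P - g·O + noise with SD 1.

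Three quantities follow:
- Effect at fixed opioid use (direct effect): -d.
- Total randomised difference: -d(1 - g·b).
- Arm coefficient from regressing Y on A and O: -d(1 - R²), where R² = 4b² / (4b² + s²) is the within-arm share of opioid variance explained by underlying pain.

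The last follows because, given A and O, the expected value of U is λ(O - 5b + b·d·A), with λ = 4b / (4b² + s²). The arm coefficient is then -d + λ·b·d, and λ·b = R². The fitted opioid coefficient is λ - g.

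The adjusted coefficient does not contain g, the potency of the opioid. The masking caused by rescue is d·g·b, which depends on g. The regression therefore cannot reveal how much was masked.

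**Numbers for d = 1.5** (absolute differences in points):

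| b | s | R² | Adjusted | Total, g = 0 | Total, g = 0.3 | Total, g = 0.6 |
|---|---|---|---|---|---|---|
| 0.5 | 1 | 0.5 | 0.75 | 1.50 | 1.275 | 1.05 |
| 0.5 | 2 | 0.2 | 1.20 | 1.50 | 1.275 | 1.05 |
| 1 | 1 | 0.8 | 0.30 | not run | 1.05 | 0.60 |
| 1 | 2 | 0.5 | 0.75 | not run | 1.05 | 0.60 |

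A simulation of 1,000,000 patients per setting agrees to within about 0.01.

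- **Range.** Adjusted 0.30 to 1.20, total 0.60 to 1.50, direct effect 1.50 throughout. With d = 1 the simulated ranges are 0.19 to 0.80 adjusted, 0.40 to 1.00 total, and 1.00 direct.
- **Direction.** The adjusted value is below the total in eight of the ten settings. It is above in two, both with g = 0.6 and s = 2: 1.20 against 1.05, and 0.75 against 0.60. The reversal occurs when g·b exceeds R².
- **Opioid coefficient.** With b = 1, s = 1, g = 0.3 it is 0.8 - 0.3 = +0.5, although the true effect is -0.3. Morphine would appear to raise pain.
- **Against the margin.** With b = 0.5, s = 1, g = 0.3, the simulated difference moves from -1.28 (outside ±1) to -0.76 (inside). The grid was chosen, not estimated, so the number of settings that cross the margin carries no weight.
- **No infusion effect.** With d = 0, adjusted and unadjusted differences are both about 0 in every setting.

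**Point estimate and interval.** The equivalence rule uses the interval. On the planning SD with 70 per arm, the half-width is 1.645 × 2 × √(2/70) = 0.56, so an interval fits inside ±1 only if the estimate is within about ±0.44. An estimate of -0.76 would not meet the rule. An estimate of -0.30 (b = 1, s = 1, g = 0.3, randomised difference -1.05) would, ignoring the modest change in standard error that the covariate brings.

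**The case against.** The strongest reply is that nothing decisive rests on this analysis. It is the last sentence of Data Analysis, is labelled as further work, and feeds no decision rule. Pain and morphine are each already compared between arms without adjustment, so a reader will see unequal rescue use in any case. That stands, and it limits the weight of the point. Only the combined analysis is at fault.

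The size is also open to challenge. It depends on the within-arm correlation between pain and opioid, which the article does not give. A single shrinkage factor, such as one third, would reflect one assumed correlation. Varying opioid potency would not test it, because potency drops out of the adjusted coefficient. Across the settings above, the adjusted value is 20% to 80% of the direct effect (0.30/1.50 to 1.20/1.50). This too stands: only an assumed range is supported.

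Finally, a rank-based composite is one remedy among several. It answers a different question from a difference in points. That is also correct, so it is offered below only as an option.

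None of this rescues the regression as an estimate of a treatment effect. It is a stated analysis, not a detail left to an unseen plan, and the article's own description of rescue supplies each step of the argument.

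**Conclusion.** The point holds as a defect in a further analysis. If the infusion affects pain or opioid use, the opioid-adjusted difference is neither the total randomised effect nor the effect at equal opioid use. In the assumed linear models with a direct effect of 1.5 points it lies between about 0.3 and 1.2, against a randomised difference of 0.6 to 1.5. These figures rest on linearity and on chosen values for the pain-opioid relation, not on anything in the article.

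A reader might infer three stronger things that the document does not support:
- That the equivalence test is biased. It is not, because the principal regression contains only infusion type and operation type.
- That adjustment always shrinks the difference. It usually does here, but not in every setting.
- That the estimate is biased whatever the truth. In the simulation there is no bias when the infusion has no effect, which is the trial's own hypothesis.

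What remains is a risk of interpretation: if a real benefit exists, this analysis can wrongly reassure readers that rescue did not hide it.

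**What to change.** Do not present the opioid-adjusted regression as a treatment effect. Either remove it, or keep it as explicitly exploratory with its causal assumptions written down, above all that no unmeasured factor such as underlying pain drives both opioid use and the pain score.

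Address rescue use through randomised comparisons: for each 12-hour period, report the arm differences in pain and in opioid amount together, each with a confidence interval. Both are already planned separately, so this is mainly a matter of joint presentation.

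Optionally, add a prespecified joint pain-opioid measure, for example the sum of each participant's ranks on pain and on opioid, compared between arms and stratified by operation. It is harder to read than a difference in points and has no link to the ±1 margin, so it can only support the principal analysis.

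The cost is a change of wording in the analysis plan. The data are already to be collected, and the sample size does not change.
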